### Instruments for data collection

Pre-tested, validated, semi-structured proforma will be used both pre- and post-intervention (questionnaire,
*Extended data*
^27^). The instrument will include the demographic details of the participants and Likert scores in these domains: knowledge, attitude and practices (involvement) towards IYCF.

### Data collection methodology

Necessary permissions are taken from the Head of the Institute and District Health Authorities. Two Research Assistants will be recruited from the field of Social Work, with communication skills and ability to interact with the population using the local language. After their training on implementation of the module, they will visit the study participants for the implementation.

The fathers accompanying the infants will be approached and will be provided with the participant information sheet (
*Extended data*
^27^). Written informed consent will be taken from each of them by the research assistants and they will be allocated to one of the intervention groups and one-to-one interaction for module implementation will be followed as stated above. The assessment at six months will be done by the research assistants for both the groups with respect to knowledge, attitude and involvement (practices) in their IYCF.

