### Study design

The study will be a unblinded parallel group RCT. This study will follow the Consolidated Standards of Reporting Trials (CONSORT)
^25,
26^. The study flow according to CONSORT guidelines is depicted in the
*Extended data*
^27^. This study protocol is reported along with Standard Protocol Items: Recommendations for Interventional Trials (SPIRIT) Guidelines
^28^. A completed SPIRIT checklist can be found in the
*Reporting guidelines*
^27^.

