### Sampling strategy and randomization

The study participants will be identified using multi-stage random sampling technique, wherein from each of the five Taluks of the District equal number of participants will be selected irrespective of their locality (urban or rural). Within each Taluk, one Public health institution and in the area covered by that institution, one ward (an administrative unit) will be selected using lottery technique. List of participants will be obtained from these public health institutions and number of participants from each selected ward will be decided based on probability proportionate to size. In the wards, they will be selected using convenience method till the required sample size gets covered.

Based on the findings from initial assessment at the district for level of knowledge, attitude and practices towards paternal involvement in IYCF, the areas with fathers of infants with poor IYCF practices will be mapped for visits at their households. Selected eligible participants will be allocated to modular intervention and control groups. A simple randomization technique with 1:1 allocation will follow. A lottery technique will be used for randomization, until the needed sample size is reached, with the help of Microsoft Excel software. The principal investigator will generate the sequence for randomization and another author (NK) will enroll the participants according to this sequence. The research assistants will implement the modular intervention.

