### Intervention procedure

An IYCF improvement module that has been developed as an easy to use flip chart with a blend of pictures and textual materials has been produced (IYCF module,
*Extended data*:
^27^), which included the basic aspects of infant and child nutrition and feeding: (i) assisting in feeding; (ii) changing diapers; (iii) giving a bath to the child; (iv) putting the child to sleep; (v) playing with the child and (vi) taking the child outside the home, (e.g. - for a walk).

The module was developed based on the available literature and brainstorming sessions with the researchers. All the investigators were involved in implementing the brainstorming technique and three investigators (PM, RT and PR) designed the module to the final format. The module will be implemented in the local language (Kannada).

This module will be administered to the intervention group only. The control group will receive regular care at the study centers, which is routinely made available to them whenever they visit health centres or when health workers visit them. This will not affect the ultimate results of the study. The administration of the module to the intervention group will be done monthly for six months. Both groups will be followed up at the end of six months, during which they will be assessed for the level of involvement in IYCF, which is the same method as that of pre-assessment (see questionnaire,
*Extended data*
^27^).

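### The module deliverers and the six-month assessors are the same two unmasked research assistants, and no separation between the roles is stated

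*Protocol article*

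**What the plan says.** Under Study design the article declares the trial open: "The study will be a unblinded parallel group RCT".

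The staffing is given in two places. Sampling strategy and randomization says that "The research assistants will implement the modular intervention". Data collection methodology says that "Two Research Assistants will be recruited from the field of Social Work", and then: "After their training on implementation of the module, they will visit the study participants for the implementation". The same section has the research assistants obtain written consent and ends with the outcome visit: "The assessment at six months will be done by the research assistants for both the groups".

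Contact with these staff differs by arm. Intervention procedure states that "This module will be administered to the intervention group only" and that "The administration of the module to the intervention group will be done monthly for six months". The control group has regular care only. The Abstract and Data collection methodology describe delivery as one-to-one.

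The instrument gives "Likert scores in these domains: knowledge, attitude and practices (involvement) towards IYCF". Outcomes takes all results from this proforma and names no observed measure and no report from the mother.

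**The concern.** The module teaches fathers to take part in feeding and care, and the outcome listed first is how much they say they take part. If the person asking is the one who has taught these behaviours month after month, two forces can push the score upwards. The assistant may expect improvement and record accordingly, and the father may want to show that the teaching worked. Neither force acts in the same way on a control father, who has had no module visits.

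The shift would therefore differ between arms. Randomization balances the fathers at entry but does nothing about a difference that arises when answers are given and recorded. A finding in favour of the module could then partly reflect who held the questionnaire. Fathers and deliverers cannot readily be masked here, but nothing in the design requires the deliverer to be the assessor.

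**Working it through.** **Who does what, from the text**

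| Task | Who, according to the article | Section |
|---|---|---|
| Consent | Research assistants | Data collection methodology |
| Module delivery | Research assistants (two recruited) | Sampling strategy and randomization; Data collection methodology |
| Six-month assessment, both arms | Research assistants | Data collection methodology |
| Monitoring of data | Departmental administrative staff outside the study | Data management |

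Deliverers and assessors come from one pool of two people. The text does not say which assistant assesses which father, and it states neither masking nor separation.

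**Does another part of the plan protect the result?**

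- Data management: the 10% check compares the database with the completed proforma, and the monitoring concerns the data. Neither reaches bias that is already in the answers on the form.
- Data analysis: intention to treat, t tests, chi-square tests and multiple logistic regression all take the recorded score as given. None can separate a reporting shift confined to one arm from a real change.
- Instruments: a validated proforma does not cancel the effect of who administers it.

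**Illustration of what a shift would do**

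The article gives no figure for this bias, so there is none to reproduce. Inputs:

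- Evaluable fathers per arm, n. The Abstract gives a total of 120 and Sample size gives 60. That conflict is a separate matter, so both are shown. With 20% lost: 120/2 × 0.8 = 48 and 60/2 × 0.8 = 24.
- Two-sided test at 0.05. The article states p<0.05; two-sided is assumed.
- Comparison of mean scores with equal SDs, normal approximation.
- True effect zero; the intervention-arm mean is raised by b SD through reporting or scoring alone. **The values of b are assumptions.**

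Formula: P(reject) = Φ(b/√(2/n) − 1.96) + Φ(−b/√(2/n) − 1.96).

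For b = 0.2:

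- n = 48: √(2/48) = 0.204 and 0.2/0.204 = 0.980. Φ(−0.980) + Φ(−2.940) = 0.164 + 0.002 = 0.165 after rounding.
- n = 24: √(2/24) = 0.289 and 0.2/0.289 = 0.693. Φ(−1.267) + Φ(−2.653) = 0.103 + 0.004 = 0.107.

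| Assumed shift b (SD) | 48 per arm | 24 per arm |
|---|---|---|
| 0 | 0.050 | 0.050 |
| 0.2 | 0.165 | 0.107 |
| 0.3 | 0.312 | 0.180 |
| 0.5 | 0.688 | 0.410 |

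For any given shift, the larger sample makes the false-positive risk worse.

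**The case against.** Several points on the other side have force.

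- **Pairing is not stated.** A reader might infer that every intervention father will be assessed by his own instructor. The article does not say so. One assistant could assess the fathers taught by the other without departing from the text. This stands: what the document supports is that the pairing is possible and not excluded. Even with such an exchange, both assistants would still be unmasked deliverers of the module.
- **The instrument is not shown.** The questionnaire is in the extended data. Self-report is the natural reading of Likert scores for knowledge, attitude and practice with no other source named, but who fills in the form, and with how much discretion, is unknown. Knowledge items are also less open to a wish to please than attitude and involvement items.
- **The open design is disclosed, and the same staff and method serve both arms.** This avoids having different assessors in each arm. It does not help when the assessor's prior relationship with the father differs by arm.
- **The figures depend on assumed shifts.** A reader might take 17% as the trial's actual type I error. Nothing in the document supports any particular shift. The table shows how the test behaves under a bias, not that a bias of that size exists.
- **The main outcome is not labelled primary.** Involvement comes first under Outcomes and is the subject of the aim and of the second objective, but the article does not use the term.

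It would also go too far to say that a favourable result could not be told apart from bias at all. The document supports a risk of bias in one direction, of unknown size.

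**Conclusion.** The concern holds as a stated design choice that can bias the comparison, not as an error or contradiction in the article. The two assistants who deliver the module are also the assessors in both arms, unmasked and with no separation stated. The likely direction favours the module, and no planned analysis corrects it.

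The size is unknown. Under an assumed 0.2 SD shift and no true effect, type I error would be about 17% (48 per arm) or 11% (24 per arm) in place of 5%. This rests on a comparison of means, 20% loss and an assumed shift.

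This should be fixed, as a cheap improvement.

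**What to change.** Change Data collection methodology so that:

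1. No assistant assesses a father to whom he or she delivered the module. Assign this father by father, or by Taluk if delivery was in fact divided that way; the article does not say that it was.
2. Each assistant assesses fathers from both arms, so the controls are shared between the two.
3. The assessor works without the allocation list and asks the father at the start not to mention any visits.
4. The assessor records at the end whether the arm became known.

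**Cost.** No extra staff and no change to sample size, only some rescheduling and travel. If both assistants have taught the same father, the exchange fails for him, and he would need an assessor who did not deliver the module.

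**What remains.** The exchange removes the own-instructor pairing and reduces assessor bias. The father still answers to a project worker after months of project visits, and the assistants may already know some allocations. Some social-desirability bias and unmasking will persist and should be stated as a limitation.

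**Timing.** Current status of the study reports four of the six monthly rounds given, so the change was still possible when the article was written. Whether it still is cannot be told from the document.

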### Data management

All the data collected in the field will be managed at the central coordinating site, independent of funding organization. A separate Data Monitoring Committee (DMC) will not be constituted. The filled proforma will be edited for inadvertently missing information, related to the demographic component and the participants will be contacted and for missing details. The variables will be coded and entered in IBM SPSS Statistics for Windows (Version 25.0. Armonk, NY: IBM Corp). From this database, 10% of the data will be randomly chosen to validate against the proforma. If the error rate is >0.3%, then the data re-entry will be performed. The data forms will be accessible only to the study staff. The entered data will be secured with a password protected access. The monitoring of data will be undertaken by the administrative staff of the study department and they are not part of the study.

### Data analysis

Results will be expressed as proportions, mean (with standard deviation), median (with interquartile range), using appropriate tables and figures. We will follow intention to treat analysis (ITT). The comparison for the continuous variables will be done using the “t” tests. For comparison across the groups, Chi square tests and Multiple Logistic Regression will be used and p<0.05 will be considered statistically significant.

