### Sample size

With anticipated improvement in the paternal involvement of IYCF following the modular intervention as 15%, 80% power, 95% Confidence Interval, 1:1 allocation and along with addition of 20% non-response error, the total sample size will be
**60** subjects.

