### Eligibility criteria

Fathers of infants and young children with poor involvement in IYCF in households in Dakshina Kannada District will be selected for this study. Initial assessments of all fathers from selected households (see
*Study population)* will be conducted to assess fathers’ knowledge, attitude and practices towards IYCF (see questionnaire in
*Extended data*
^27^). Fathers with scores in the lower 50
^th^ percentile in the practice domain will be categorized as fathers with poor involvement in IYCF and will be eligible for inclusion in the RCT.

Those fathers who are not available for interventions despite three attempts of contact will be excluded. To promote retention of the participants, visits will be made to them at a convenient time and location. 

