### Outcomes

The level of involvement of fathers in IYCF, which is of paramount importance to the overall nutrition of children, and extent to which the modules will achieve improvement. In addition, change in knowledge and attitude towards IYCF will be assessed at the end of six months of intervention. The outcomes assessed will be knowledge scores, attitude scores and practice (involvement) scores obtained through the proforma.

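### No baseline-adjusted analysis of the practice score is named, although a between-arm ANCOVA on data already collected would be more precise

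*Protocol article*

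**What the plan says.** The protocol's Outcomes section defines what is measured as scores: "The outcomes assessed will be knowledge scores, attitude scores and practice (involvement) scores obtained through the proforma". The Instruments for data collection section uses one proforma before and after the intervention, and the Intervention procedure section describes the six-month assessment as one "which is the same method as that of pre-assessment".

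Entry depends on the baseline practice score. Under Eligibility criteria, fathers in the lower 50th "percentile in the practice domain will be categorized as fathers with poor involvement in IYCF", and only they can be randomised. Every randomised father therefore has a baseline practice score on record.

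The Data analysis section fixes the methods: "The comparison for the continuous variables will be done using the “t” tests", and "For comparison across the groups, Chi square tests and Multiple Logistic Regression will be used", with the rule that "p<0.05 will be considered statistically significant". It does not say whether the t tests compare arms or time points, and it lists no covariates for the logistic model. It names no linear model of the score that includes baseline.

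**The concern.** Two things are at stake.

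**Precision.** A baseline measurement of the outcome is often among the best predictors of its follow-up value. A t test on six-month scores leaves that information unused. Chi-square and logistic analyses can take a score only after it has been cut into categories, which discards more. As written, the same outcome can also be tested as a score and as a category, each at the 0.05 level.

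**Which comparison is made.** The wording keeps the phrase about comparing groups for the categorical methods, so the t tests could be read as before-and-after tests within an arm. The Sample size section also speaks of improvement after the intervention: "With anticipated improvement in the paternal involvement of IYCF following the modular intervention as 15%, 80% power, 95% Confidence Interval, 1:1 allocation". Because fathers enter on a low practice score, their mean would be expected to rise at a second measurement even if the module did nothing. A paired test in the intervention arm would credit that rise to the module.

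**Working it through.** **The plan's own figures.** The protocol gives no standard deviation, correlation or follow-up cut-point, so there is no figure on this point to reproduce. The nearest is the sample size. With an assumed control rate of 0% against 15%, two-sided, the requirement is 48 per arm, and 48/(1 − 0.2) = 60 per arm, or 120 in total. That matches the Abstract but not the total of 60 in the Sample size section. This conflict is a separate matter, and the results below do not depend on which total is right.

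**Assumptions.** Scores are normal. The correlation ρ between baseline and six months, before selection, is 0.3 to 0.8. Entry is restricted to baseline scores below the median. Tests are two-sided at 0.05.

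**Step 1: effect of selection.** Keeping only the lower half shrinks the baseline variance to k = 1 − 2/π = 0.363 of its original value. The squared correlation among those selected is

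r² = ρ²k / (ρ²k + 1 − ρ²),

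and the ANCOVA residual variance, relative to a t test on six-month scores, is 1 − r². For ρ = 0.7: 0.49 × 0.363 = 0.178; r² = 0.178 / (0.178 + 0.51) = 0.259; variance factor 0.741.

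**Step 2: power.** A t test with 80% power corresponds to 1.960 + 0.842 = 2.802 standard errors. With ANCOVA, power is Φ(2.802/√(1 − r²) − 1.960), ignoring the one degree of freedom spent. For ρ = 0.7: 2.802/0.861 − 1.960 = 1.295, or 90%.

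| ρ before selection | ANCOVA variance factor | Power, from 80% | Fathers equivalent to 120 | Fathers equivalent to 60 | Change-score variance factor |
|---|---|---|---|---|---|
| 0.3 | 0.965 | 81% | 116 | 58 | 1.154 |
| 0.5 | 0.892 | 84% | 107 | 54 | 1.000 |
| 0.7 | 0.741 | 90% | 89 | 45 | 0.789 |
| 0.8 | 0.608 | 95% | 73 | 37 | 0.632 |

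The last column is ((1 − ρ)²k + 1 − ρ²) / (ρ²k + 1 − ρ²). Leaving selection out would overstate the ANCOVA gain, with factors of 0.91, 0.75, 0.51 and 0.36.

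**Step 3: cutting the score.** A normal score cut at its median keeps 2/π = 0.64 of the information, a loss of about 36%. Power of 80% falls to Φ(2.802 × √0.637 − 1.960) = Φ(0.276), about 61%. Other cut-points give other losses.

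**Step 4: regression to the mean.** Without any effect, each arm rises on average by (1 − ρ)√(2/π) SD of the unselected score: 0.40 at ρ = 0.5 and 0.24 at ρ = 0.7. A simulation of 10,000 trials per setting with no true effect, at 30 and 60 per arm and ρ = 0.5 and 0.7, gave these rejection rates:

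- Between-arm t test on six-month scores: 5.0% to 5.2%, with bias near zero.
- Between-arm t test on change: 4.9% to 5.1%.
- ANCOVA: 4.8% to 5.2%. With 60 per arm its standard error was 0.159 against 0.168 for the t test at ρ = 0.5, and 0.131 against 0.152 at ρ = 0.7.
- Paired t test within the intervention arm: 40% to 63% with 30 per arm, and 70% to 92% with 60 per arm.

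**The case against.** The strongest reply is that a between-arm t test in a randomised trial is valid, that this is a condensed article, and that covariates and the type of t test are often settled elsewhere. That stands as far as it goes: a missing covariate list is not the point here. What remains is that the section does name its methods, and none of them is a baseline-adjusted analysis of the score it will hold.

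Three stronger readings are tempting, and the documents support none of them.

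- **That the named methods force the score to be cut.** They do not. The t tests are assigned to continuous variables and need no cut. The loss in Step 3 applies only to a chi-square or logistic analysis of the score in categories.
- **That the plan ignores baseline altogether.** This is not shown. A multiple logistic regression could include the baseline score, and a t test on change would use it. At ρ = 0.7 to 0.8 the change score recovers most of the ANCOVA gain. At 0.5 it gains nothing, and at 0.3 it is worse than the plain t test.
- **That regression to the mean biases the trial's comparison.** It does not. Fathers are randomised 1:1 and both groups are assessed at six months in the same way, so both arms regress equally. The control arm gives the protection. ANCOVA adds precision and corrects for chance baseline imbalance. The harm arises only if the t tests are run within arm, which the text leaves open but does not state.

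**Conclusion.** The point holds as one of efficiency and clarity. It does not show that the planned between-arm comparison is invalid. ANCOVA would reduce residual variance by about 4% to 39%, depending on a correlation that the documents do not give. At the low end the gain is slight; at the high end it would let 73 fathers do the work of 120. The figures rest on normal scores and selection at the median. A summed Likert score may depart from normality, which would move the numbers but not the direction. The within-arm risk is conditional on how the t tests are meant, but would be serious if realised, and one sentence removes it.

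**What to change.** Amend the Data analysis section as follows:

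- **Primary analysis:** one between-arm ANCOVA of the six-month practice score on arm and baseline practice score, reported as an adjusted mean difference with 95% confidence interval. Adjustment for Taluk is optional.
- **Secondary outcomes:** knowledge and attitude scores, each analysed in the same way with its own baseline.
- **Supportive:** chi-square and logistic analyses of involvement in categories, with the cut-point stated in advance.
- **Descriptive only:** within-arm changes from baseline, with no test used as evidence of effect.

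The cost is wording only, since every variable is already collected. The Current status section reports recruitment complete and four of the six monthly rounds given, so on that account the change could still be dated and recorded before six-month scores are seen.
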